#### Cost-consequence analysis

A cost-consequence analysis will be performed from a Canadian single-payer perspective. This will include assessing the purchasing, installation, and maintenance costs associated with the far-UVC lights; testing and treatment costs for RVIs, photokeratitis, and erythema; and the effects (consequences) associated with the intervention compared to the alternative. Outcome and patient characteristics data will come from the trial. Testing and treatment costs per case associated with the outcomes, including adverse outcomes, will come from the Canadian Institute for Health Information patient cost estimator [46], complemented with cost data from the literature. The analysis will involve estimating risk differences associated with RVIs, photokeratitis, and erythema between the intervention and control groups, using the augmented-inverse probability of treatment weighting models with a lasso for variable selection. Sensitivity analysis will be performed using a generalized linear model for the binomial family. Differences in mean testing and treatment costs between the two groups will be estimated using a two-part model.

Statistical analysis in Phase 2 is unchanged from Phase 1.

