### Intervention description {11a}

LTC facility neighborhoods randomized to the intervention arm receive far-UVC light devices in addition to mandated infection control interventions. The far-UVC light devices are approximately the size of a smoke detector. They are installed on the ceiling in high traffic common areas in LTC facilities, where residents spend approximately 3 to 4 h per day. The lights are on 24 h per day throughout the data collection period of the study. The devices produce no heat, and the only indicators of operation are an indicator LED and a dim blue light from a square in the center.

At the onset of Phase 1, the threshold limit value (TLV) set by the American Conference of Governmental Industrial Hygienists (ACGIH) for 222-nm far-UVC was 23 mJ/cm^2^ per 8-h working day. The far-UVC devices used in Phase 1 emit 222-nm light, at an 80° beam angle, with an output tuned to meet this TLV at a height of 2.1 m from the floor for a standard 2.7-m ceiling. Since the start of Phase 1, ACGIH has updated 222-nm far-UVC TLVs to 160 mJ/cm^2^ per 8 h for eye exposure and 479 mJ/cm^2^ per 8 h for skin exposure [28].

The American National Standards Institute (ANSI) and Illuminating Engineering Society (IES) have adopted ACGIH’s new TLVs in their ANSI/IES RP-27.1–22 standard. To reflect these updated photobiological limits, the far-UVC devices will be replaced in Phase 2. The new devices (1) emit higher irradiance to achieve higher doses than Phase 1, (2) are equipped with an optical filter to attenuate UVC wavelengths above 23 nm, and (3) are equipped with a diffuser to increase the beam angle to 108°.

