## Statistical methods

### Statistical methods for primary and secondary outcomes {20a}

#### Descriptive analysis

Means, proportions, and medians will be produced with corresponding measures of variability (standard deviation and interquartile range) for key patient characteristics for the whole population and stratified by treatment assignment, neighborhood clusters, and site. Stage-wise heterogeneity in the descriptive statistics before and after adaption of the new lamps will also be explored. Kaplan–Meier curves will be used to illustrate trends in infection probabilities and a log-rank test will be used to estimate the crude difference in probability of RVI between the treated and control group, stratified by neighborhood clusters and site.

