#### Primary analysis

The primary analysis will be an intention-to-treat effect estimated via comparison of 3-year incidence of COVID-19 or RVIs among individuals assigned to each treatment group. We will use a Cox model, which has the flexibility to account for the clustered nature of the data and adjust for prognostic factors, to estimate the hazard ratio. We will account for clustering within neighborhoods and by site using mixed-effects models [43]. Prognostic factors, at the individual (i.e., age, sex and frailty) will be explored and potentially adjusted for [44]. It is recommended that cluster-level prognostic factors are also adjusted for incluster randomized trials; however, we do not anticipate much variation here.

The change in lamps in Phase 2 present some unique analytical challenges. Participants in Phase 2 will presumably experience higher levels of far-UVC exposure. We will explore whether infection rates change between the two phases and will likely add a binary indicator to divide the person-time contributed into Phase 1 and Phase 2.

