### Methods for additional analyses {20b}

There are no subgroup analyses planned.

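### The only between-arm estimate stated for erythema and photokeratitis pools two lamps of different dose, while the split by lamp phase is given for infections only

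*Protocol article*

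**What the plan says.** All references are to the protocol article.

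- **Harms as outcomes.** Outcomes {12} lists the incidence of erythema and of photokeratitis among the secondary outcomes. Section {18a} has facility staff collect both at daily routine examinations.
- **How the arms are compared.** The Secondary analysis text deals only with the screening tools, and section {22} covers recording and escalation of adverse events. The between-arm comparison appears under Cost-consequence analysis, where the planned estimates are "risk differences associated with RVIs, photokeratitis, and erythema between the intervention and control groups, using the augmented-inverse probability of treatment weighting models with a lasso". A binomial generalized linear model is the sensitivity analysis. No phase term is given for either.
- **The lamps.** Under {11a}, the Phase 1 devices had a limit of 23 mJ/cm² per 8-hour day and were built "with an output tuned to meet this TLV at a height of 2.1 m from the floor". The limits later became 160 (eye) and 479 (skin), and the article draws the consequence: "To reflect these updated photobiological limits, the far-UVC devices will be replaced in Phase 2". Three differences are then listed. The replacement lamps carry an optical filter, have a diffuser that widens the beam, and "emit higher irradiance to achieve higher doses than Phase 1".
- **Where phase does enter.** Primary analysis: "We will explore whether infection rates change between the two phases and will likely add a binary indicator to divide the person-time". Descriptive analysis: "Stage-wise heterogeneity in the descriptive statistics before and after adaption of the new lamps will also be explored". The latter follows a sentence on key patient characteristics and does not name harms.
- **General statements.** "Statistical analysis in Phase 2 is unchanged from Phase 1" closes the cost-consequence text, and section {20b} says "There are no subgroup analyses planned".

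**The concern.** The article recognises that the change of lamp complicates the analysis, because residents in Phase 2 will presumably receive more far-UVC, and it responds for infections. The same reasoning applies at least as directly to skin and eye harms, for which dose is the obvious driver and the filter a plausible protection. Yet the comparison stated for these two outcomes treats both lamps as one intervention.

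A facility deciding whether to install far-UVC would install something like the Phase 2 device. A risk difference pooled over both devices does not answer for it: a harm confined to the new lamp would be diluted by time under the old one, and a gain in safety from the filter would be masked in the same way. Section {22} rests its view that the risks are minimal partly on dose, and section {24} rests the altered consent on minimal risk. Dose is one of the things that changed.

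**Working it through.** **1. Is there a figure in the plan to reproduce?** Not for these harms: no expected rate, precision or sample size is stated. The figures under Sample size {14} concern the primary outcome. The only input taken from there is the anticipated total of about 500 residents, hence about 250 per arm if the arms are equal (an assumption).

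**2. What is stated, side by side.**

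| Outcome | Between-arm estimate stated | Phase split stated |
|---|---|---|
| Infections | Cox hazard ratio; also a cost-consequence risk difference | Yes for the Cox analysis: a phase indicator on person-time, described as likely |
| Erythema, photokeratitis | Cost-consequence risk difference, with a binomial model as sensitivity analysis | None |

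**3. What changed between lamps.** Ratios of the exposure limits in {11a}:

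- eye: 160 / 23 = 6.96
- skin: 479 / 23 = 20.8

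These are ratios of permitted exposure. The Phase 2 dose is described only as higher, with no number.

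**4. What pooling does.** If a share *s* of the pooled active arm reflects the Phase 2 lamp, the pooled risk is *s* × r₂ + (1 − *s*) × r₁. The document gives neither *s* nor the risks, so the values below are assumed for illustration only.

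| Share under Phase 2 lamp | r₁ = 0, r₂ = 2% | r₁ = 2%, r₂ = 0 |
|---|---|---|
| 30% | 0.6% | 1.4% |
| 50% | 1.0% | 1.0% |
| 70% | 1.4% | 0.6% |

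The middle column is a harm of the new lamp diluted; the last is a safer new lamp made to look harmful. At equal shares the two opposite situations give the same pooled number.

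**5. What a phase-specific report costs in precision.** Take zero events among *n* residents as the reference case. The exact two-sided 95% upper bound is 1 − 0.025^(1/n):

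- n = 250 (whole active arm): 1.46%
- n = 180 (assumed seen under the Phase 2 lamp): 2.03%
- n = 125 (assumed seen under the Phase 2 lamp): 2.91%

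**6. Effect of clustering on such bounds.** The exact bound treats residents as independent. As an approximation, divide *n* by the design effect 1 + (m − 1) × ICC. The article supports 11 neighborhoods (six plus five, from {9}) or 21 (sixteen plus five, from {16a}), so m is about 500 / 11 = 45 or 500 / 21 = 24. The ICC for harms is assumed.

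| m | ICC | Design effect | Effective n (from 250) | Upper bound |
|---|---|---|---|---|
| 24 | 0.01 | 1.23 | 203 | 1.80% |
| 45 | 0.01 | 1.44 | 174 | 2.10% |
| 24 | 0.05 | 2.15 | 116 | 3.12% |
| 45 | 0.05 | 3.20 | 78 | 4.61% |

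Phase-specific bounds would widen similarly, which is why a listing by neighborhood should accompany them.

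**The case against.** The strongest reply is that this is silence in a condensed article. A full protocol is available on request ({31c}) and a Phase 2 addendum exists (Trial status). Neither is shown, and the layout of safety tables often belongs in such documents. The quoted estimate also serves an economic comparison; nothing says the safety conclusion will rest on it. This stands in part: it limits the point to what this document states. But the document does fix an estimator for these named secondary outcomes and does address the lamp change for infections, so the asymmetry is on the page.

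Five stronger readings are tempting and are not supported:

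- **That a split by lamp is ruled out.** A reader might infer this from "Statistical analysis in Phase 2 is unchanged from Phase 1" and "There are no subgroup analyses planned". Both stand beside the phase indicator proposed under Primary analysis, so the authors evidently do not read them as a bar. Phase also divides person-time and does not define a subgroup of residents.
- **That residents receive 7 or 21 times the dose.** Those are ratios of limits. The delivered dose is not given, and {11a} puts residents in the lit areas for about 3 to 4 hours a day against limits set per 8 hours.
- **That pooling hides a harm.** The filter could lower the risk, so the direction is open.
- **That the method is wrong because it gives no usable interval with zero events.** This is conditional. Background erythema may well produce events, and an analyst facing a zero count would supply an exact bound in any case. Nor should the model be confined to harms with events in both arms: a purely device-caused harm would leave the control arm empty, and the comparison would be dropped where it matters most.
- **That harms would go undetected.** Section {22} has residents screened daily and significant events escalated individually.

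**Conclusion.** The point holds as a gap in the reported comparison, worth a cheap improvement. For both harms, the only between-arm estimate stated in this document mixes two devices that differ in dose, filtering and beam. It cannot be read as the safety of the Phase 2 lamp. The sign and size of the resulting distortion cannot be derived from the document; the pooling illustration rests on assumed risks and shares.

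The precision figures assume 250 residents per arm and independence between residents, and for Phase 2 an assumed 125 to 180 active-arm residents. An undisclosed addendum or analysis plan may already contain the split. If so, the remaining action is to say so where the harm estimate is described.

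**What to change.** 1. Extend the phase division of person-time proposed under Primary analysis to erythema and photokeratitis.
2. For each harm, report residents affected, resident-time and rates by arm and by lamp phase, with exact 95% bounds and a listing by neighborhood, since the exact bounds ignore clustering.
3. Base the safety statement on the Phase 2 data, comparing the arms within that phase.
4. Keep the pooled risk difference, with its binomial sensitivity analysis, for the cost-consequence table, and label it as covering both lamps.

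This takes a few lines of wording and one or two tables, from data already collected daily. The real cost is precision: with no events, the upper bound moves from 1.46% for the whole active arm to between 2.0% and 2.9% under the assumed Phase 2 numbers, and further once clustering is considered. That is acceptable, because the wider bound applies to the lamp that would be adopted.

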### Interim analyses {21b}

There are no interim analyses planned to preserve power of the final analysis.

### Methods for additional analyses {20b}

There are no subgroup analyses planned.

### Methods in analysis to handle protocol non-adherence and any statistical methods to handle missing data {20c}

The nature of the intervention is such that non-adherence is infeasible.

### Plans to give access to the full protocol, participant level-data and statistical code {31c}

The datasets analyzed during the current study and statistical code are available from the corresponding author on reasonable request, as is the full protocol.

## Oversight and monitoring

### Composition of the coordinating center and trial steering committee {5d}

Research coordinators at the Nova Scotia Health Geriatric Medicine Research team oversee the day-to-day running of the trial. The Scientific Advisory Council for this trial monitors data quality and safety of the study protocols with quarterly meetings. The Scientific Advisory Council is composed of representatives from the Nova Scotia government Department of Seniors and Long-Term Care, the Nova Scotia government Department of Public Health, the Dalhousie University Department of Civil and Resource Engineering, and the Dalhousie University Division of Infectious Diseases.

There is no discrete Stakeholder and Public Involvement Group. However, monthly newsletters are sent to LTC home residents and their family members to provide updates about the study. Each newsletter contains a survey to solicit feedback about residents’ experiences with study participation.

### Composition of the data monitoring committee and its role and reporting structure {21a}

Data quality is monitored by three parties: the main study coordinator, independent consultant biostatisticians, and a biostatistician on the Geriatric Medicine Research team who is otherwise not involved in the study.

### Adverse event reporting and harms {22}

All adverse events reported by participants or observed by the research team are recorded. Based on available data, there are theoretical risks of photokeratitis and skin erythema, but the dose and duration of exposure to UVC light make these risks minimal. Participants are screened daily for adverse events. If any significant adverse events occur, they are addressed immediately by the participant’s medical team and reported to the Scientific Advisory Committee and the Research Ethics Board to determine whether changes to the protocol need to be made.

### Frequency and plans for auditing trial conduct {23}

All research conducted at Nova Scotia Health is monitored and can be reviewed by Research Ethics Board auditors at any time.

### Plans for communicating important protocol amendments to relevant parties (e.g. trial participants, ethical committees) {25}

The research team has and will continue to keep participants, their substitute decision-makers, and LTC facility staff up to date about changes to the trial protocol with regular newsletters. Any amendments to the trial protocol will be submitted for approval by the Nova Scotia Health Research Ethics Board.

### Dissemination plans {31a}

Knowledge translation will include media engagement, peer-reviewed presentations, and publications of trial results.

## Ethics

### Ethics approval and consent to participate {24}

The protocol has been approved by the Nova Scotia Health Research Ethics Board. In this study, LTC facility residents are research participants because (1) they are exposed to study procedures: far-UVC light and the RVI screening protocol, and (2) their private identifiable data are collected. LTC facility staff and visitors are exposed to the intervention but cannot feasibly be randomized. Therefore, their data are not collected.

The far-UVC light intervention qualifies for an alteration of consent because it poses minimal risk and it is a cluster-level intervention, making it infeasible for LTC residents to decline exposure [47]. As a form of notification, regular newsletters disclosing the details of the study are sent to LTC facility stakeholders (residents, staff, and family caregivers), and posters describing the study are in common areas within the LTC facilities.

Researchers seek informed consent for the data collection from residents or their SDM. In lieu of formal capacity assessments, existing medical records of clinical decision-making capacity will be consulted. If a patient has documented decision-making capacity for clinical decisions, informed consent for data collection is sought from them directly. If they did not have clinical decision-making capacity, their SDM is approached to seek surrogate consent for data collection. This method of capacity assessment is appropriate because data collection procedures in this trial are akin to procedures in routine care [48].

## Discussion

The effectiveness of standard infection control measures is suboptimal in LTC facilities. If effective, far-UVC light could provide a valuable layer of protection from RVIs for LTC facility residents.

### Pragmatism

This trial has pragmatic intent [49], in that it aims to inform clinical decisions of whether far-UVC light should be implemented in LTC facilities to reduce the incidence of RVIs. Analyzing the features trial design using the PRagmatic Explanatory Continuum Indicator Summary (PRECIS)-2 tool demonstrates that the trial is highly pragmatic (Fig. 2) [50]. Trial eligibility criteria, recruitment, setting, flexibility (delivery), and flexibility (adherence) are highly pragmatic because they are consistent with how the intervention is intended to be used in clinical practice. The primary outcome is highly pragmatic because it is highly clinically relevant. The primary analysis is highly pragmatic because it is intention to treat. Organization and follow-up are rather pragmatic, because the presence of additional research nurses and additional monitoring of vitals in infected patients are slight deviations from routine clinical practice. Overall, the design of the trial is consistent with the pragmatic goal to produce evidence to inform a clinical decision. It conforms too with recommendations to broaden the evaluation of frailty status in relation to pandemic illness [51, 52], and understanding vaccine effectiveness in the common and at-risk population of older people who live with frailty [53], especially those who reside in LTC facilities [54].

**Fig. 2 Fig2:**
[figure not shown]
PRECIS-2 diagram analyzing trial design features on the explanatory-pragmatic spectrum

### Vulnerabilities

LTC residents are commonly identified as a potentially vulnerable population of research participants [55]. Nix and colleagues developed a framework to identify and mitigate vulnerabilities arising in cluster randomized trials in LTC facilities [48]. Applying the framework demonstrates that the implemented additional ethical protections appropriately addressed each vulnerability (Table 2). Further, the ethical protections of gatekeeper permission and stakeholder engagement helped integrate research procedures into the clinical setting, promoting the pragmatic goals of the trial [25].

**Table 2 Tab2:** Vulnerabilities and corresponding additional ethical protections

Ethical principle	Vulnerability	Additional ethical protection
*Autonomy*	Inadequate understanding in informed consent	Records of clinical decision-making capacity consulted in lieu of formal research capacity assessments Surrogate consent obtained from SDMs for residents lacking decision-making capacity
	Inadequate voluntariness in informed consent	Informed consent obtained by researchers with LTC facility administrators present, to make clear that participation is voluntary
	Invasion of privacy	Exposure to the intervention only in common areas Data collection procedures in residents’ bedrooms performed by LTC facility staff, as part of routine care Stakeholder engagement with pre-trial interviews and ongoing newsletters and surveys
*Welfare*	None—the study intervention and data collection procedures pose no more than minimal risk to participants	Not applicable
*Justice*	Unjust impact on care of nonparticipants	Gatekeeper permission obtained from LTC facility administrators Stakeholder engagement with pre-trial interviews and ongoing newsletters and surveys

### Limitations

A potential challenge is that LTC facility staff and visitors cannot feasibly be randomized. This poses a risk of contamination between study arms. However, there is some evidence to suggest that far-UVC light devices provide effective disinfection even as viral particles are continuously introduced into a space [16]. For this intervention, real-world effectiveness includes the ability to eliminate viral particles introduced into LTC facilities from visitors and staff who enter the space transiently. This potential contamination might hinder the internal validity of the trial, but it could simultaneously promote external validity.

The limited number of clusters and uncertainty in the survival probability have already resulted in challenges with determining of the appropriate sample size. We hope to have addressed the issue by adding an additional site and extending the study period; however, this will need to be re-examined at the 2-year timepoint, and it may be that additional sites will need to be added.

Another potential limitation is that far-UVC devices are not installed in resident bedrooms. This could hinder the effectiveness of the intervention, especially in bedrooms shared by two residents. However, limiting the intervention to common areas is justified by safety and ethical considerations. It mitigates the risk of adverse effects because (1) the far-UVC light devices emit a dose that is minimal risk for 8 h of exposure per day, which would be exceeded if residents were exposed overnight, and (2) the risk of photokeratitis is theoretically higher when lying supine, as residents are likely to do in their bedrooms. Further, limiting the intervention to common areas promotes residents’ privacy interests [48]. Finally, at current pricing, it is not financially feasible to obtain enough far-UVC devices to cover all bedrooms without industry support, which we have declined.

